##### Sample size justification

Provider implementation fidelity serves as our primary outcome used to estimate sample size given its role in linking provider behavior to client mental health [84, 94–96]. We estimate that approximately six mental health providers will enroll per center, or about 540 providers total. Power was computed to test the null hypotheses of no difference between Materials Only and Direct Training and between Direct Training and Local Supervision in a cluster trial. For the primary implementation outcome, the change from baseline to 8-month follow-up was estimated as 0.14 for the Direct Training strategy and its variance was estimated as 0.0439 using data obtained from the waitlist-controlled trial [57]. Thus, the standardized change for the Direct Training strategy was estimated at 0.67. With a 0.025 Type I error rate, allowing for two primary comparisons between the three strategies, we will have 80% power to detect an effect of *d* = 0.34–0.46 on the 8-month change of the primary outcome, assuming a between-center ICC ≤ 0.1. In other words, we will have 80% power to detect the difference between Materials Only and Direct Training when the standardized change for Materials Only is ≤ 0.21–0.33, and we will have 80% power to detect the difference between Direct Training and Local Supervision when the standardized change for the Local Supervision strategy is ≥ 1.01–1.13.

#### Moderation analyses

To identify center- and provider-level determinants of implementation success, we will use stepwise regression [97], using 8-month simulated practice skills assessment of implementation fidelity as the primary outcome. Stepwise regression will iteratively add and remove each of the implementation determinants described previously and their interaction with implementation strategy to identify the subset of determinants with the minimal Akaike information criterion (AIC) [98]. We will re-run this analysis with each of the secondary implementation outcomes.

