#### Mental health providers

Following randomization, mental health providers working at or affiliated with enrolled LGBTQ community centers will be invited to register for the training. Eligible providers must (1) be 18 years or older; (2) provide or be planning to provide mental/behavioral health services (e.g., therapy, support groups, case management) to LGBTQ clients; and (3) be affiliated with an enrolled LGBTQ community center. In order to meet the third criterion, providers may either be employed or volunteer at a participating LGBTQ community center or be in the referral network of a participating LGBTQ community center (i.e., receive referrals or intending to receive referrals of mental health clients from the center). Mental health providers will be recruited by center leadership. Upon randomization, center leaders will distribute flyers to their employees, volunteers, and referral network providers to inform them of the study/training opportunity. Center directors will be asked to share information about the benefits of the study/training (e.g., continuing education credits, free training materials, financial incentive for assessments).

To be eligible to attend the training, mental health providers must provide consent and complete the baseline survey. Upon training launch, enrolled providers will be given instructions on how to access their respective training materials and, if applicable, live webinar training sessions. Regardless of their engagement with their respective training intervention or whether they remain affiliated with an LGBTQ community center, all providers will be contacted to complete follow-up surveys at 4-, 8-, 12-, and 24-months post-baseline. No concomitant interventions are prohibited for mental health providers enrolled in the trial.

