### Implementation outcomes

In Aim 1, we will assess the implementation success of three LGBTQ-affirmative CBT implementation strategies across the 90 LGBTQ community centers. The primary implementation outcome is provider fidelity to LGBTQ-affirmative CBT using our validated “simulated practice” assessment [64]. Providers will watch two brief (3-minute) video clips of an SGM actor roleplaying a presenting concern and then briefly describe in writing the clinical approaches they would use to address the concern. Research assistants will then code responses to assess participants’ application of LGBTQ-affirmative CBT skills using our reliable (ICC = 0.87) and valid rating scheme (57). Secondary implementation outcomes include mixed-methods assessments of the reach, adoption, familiarity, modification, and maintenance of LGBTQ-affirmative CBT skills across centers (See Table 1 for operationalizations).

**Table 1 Tab1:** Measures

Outcomes	Measures	Data Source	Time point
Primary outcomes			
Implementation fidelity	∙ Simulated practice assessment [57] based on previous EBP research [117–120].	Provider simulated practice assessment	baseline, 4 m, 8 m, 12 m, 24 m
Secondary outcomes			
Reach	∙ Percentage of active clients who receive the EBP will be self-reported in provider surveys. Semi-structured qualitative interviews with providers will highlight reasons for stronger or weaker reach.	Provider surveys and qualitative interviews	4 m, 8 m, 12 m, 24 m
Adoption	∙ Percentage of providers who self-report practicing LGBTQ-affirmative CBT out of total who were trained. Semi-structured qualitative interviews with providers will highlight why and in what cases providers chose not to implement.	Provider surveys and qualitative interviews	baseline, 4 m, 8 m, 12 m, 24 m
Implementation	∙ Confidence with and use of LGBTQ-affirmative CBT skills will be measured using a scale adapted from the Counselor Activity Self-Efficacy scale [121] and Use of LGBTQ-affirmative CBT skills scales [57]. ∙ Modification of LGBTQ-affirmative CBT will be assessed by the Modification and Adaptation Checklist [122] and semi-structured qualitative interviews with providers.	Provider surveys and qualitative interviews	baseline, 4 m, 8 m, 12 m, 24 m

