#### Mediation analyses

We will assess client mental health as a function of our three implementation strategies as mediated through provider and organizational targets. We hypothesize that organizational (e.g., norms about LGBTQ-affirmative CBT) and provider (e.g., LGBTQ-affirmative CBT self-efficacy) targets will mediate the impact of implementation strategies on implementation success, and further on client mental health. We will use the difference approach [101] for multilevel mediation [102] of center-level implementation strategy on 8-month follow-up provider-level implementation fidelity through our hypothesized organizational and provider targets measured at 4-month follow-up. We will parse the implementation strategies’ total effect on the implementation outcome into direct and indirect (mediated) effects. Specially, we will fit a mixed-effects model of the implementation strategies on implementation outcome for the total effect and fit another mixed-effects model of the implementation strategies on implementation outcome plus center-level targets and provider-level targets. The fixed effects of the first model include the implementation strategies, baseline implementation fidelity, and baseline organizational and provider targets, and the second model replaces baseline organizational and provider targets with 4-month follow-up targets; random effects include center. The indirect effect is the difference between the estimated coefficients of implementation strategies between the two models; significance will be tested using bootstrapping [103]. We will use the same multilevel approach to test mediation of the association between implementation strategy and 12-month follow-up client-level PHQ-9. We will fit two mixed-effects models to estimate the total, direct and indirect (mediated) effects. The fixed effects of the first model include the implementation strategies, baseline PHQ-9, baseline implementation fidelity, and baseline organizational and provider targets, and in the second model, the baseline organizational and provider targets are replaced with 4-month follow-up targets and baseline implementation fidelity is replaced with 8-month follow-up implementation fidelity; the random effects include center and provider. We will re-run these analyses with 24-month follow-up PHQ-9 to determine maintenance of effects.

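### The Aim 2 stepwise regression leaves out the baseline fidelity score, so main effects of traits that merely go with skill at entry can be selected as determinants of implementation success

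*Protocol article*

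**What the plan says.** The Moderation analyses section states the purpose ("To identify center- and provider-level determinants of implementation success"), the outcome ("using 8-month simulated practice skills assessment of implementation fidelity as the primary outcome") and the candidate terms: "Stepwise regression will iteratively add and remove each of the implementation determinants described previously and their interaction with implementation strategy". The subset with the smallest AIC is kept, and the search is repeated for each secondary implementation outcome.

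The determinants are described under Implementation moderators and in Table 1: inner setting, outer setting, intervention characteristics, individual characteristics and implementation process. Baseline fidelity is in none of these. Table 1 lists the fidelity measure under primary outcomes, with source and schedule "Provider simulated practice assessment baseline, 4 m, 8 m, 12 m, 24 m".

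The other uses of this outcome take account of the starting level:
- The Aim 1 model is a repeated-measures mixed model with time and time-by-strategy terms.
- The provider sample size is set on change from baseline to 8 months.
- The mediation analysis takes 8-month fidelity as its outcome and writes out the covariate: "The fixed effects of the first model include the implementation strategies, baseline implementation fidelity, and baseline organizational and provider targets".

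**The concern.** In Aim 1, randomization balances entry skill across strategies in expectation. In Aim 2 the variables of interest are not randomized. Prior EBP experience, attitudes to EBPs, staff attributes and demographics may all go with how well a provider handles the simulated cases before any training. If 8-month fidelity depends on baseline fidelity, such a trait predicts the 8-month score even when it has no bearing on what happens after entry. The search can then report it as a determinant of implementation success.

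The Dissemination section promises center directors an account of barriers and facilitators, and of which strategy suits which center conditions. The first rests largely on determinant main effects, the terms exposed to this problem. The second rests on strategy-by-determinant interactions, which are not biased by the omission but are estimated with more residual variance than the collected data require.

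**Working it through.** The Moderation analyses section gives no figure to reproduce. As a check on the surrounding text, the standardized change in the provider sample size section is 0.14 / sqrt(0.0439) = 0.668, which agrees with the stated 0.67.

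**Inputs from the protocol article:** about 540 providers (90 centers, six each), three equal arms, selection by minimal AIC, rating ICC 0.87.

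**Assumptions, not in the documents:** correlation a of a determinant with baseline fidelity, 0.1 to 0.4; correlation rho of baseline with 8-month fidelity, 0.3 to 0.7. The determinant has no effect on 8-month fidelity given baseline.

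**Selection rule.** Adding a one-degree-of-freedom term lowers AIC when its likelihood-ratio statistic exceeds 2. For a truly null term, P(chi-square on 1 df > 2) = 0.157.

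**Without baseline in the model.** The within-arm correlation of determinant and outcome is r = a × rho. The statistic is then approximately noncentral chi-square with noncentrality N r² / (1 − r²). Example with a = 0.3, rho = 0.5: r = 0.15, noncentrality = 540 × 0.0225 / 0.9775 = 12.43, and P(> 2) = 0.98.

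Simulated selection rates (1,000 runs per setting, N = 540, no clustering, determinant added to a model containing strategy):

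| a | rho 0.3 | rho 0.5 | rho 0.7 |
|---|---|---|---|
| 0.1 | 27% | 42% | 59% |
| 0.2 | 49% | 81% | 96% |
| 0.3 | 76% | 98% | 100% |
| 0.4 | 92% | 100% | 100% |

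The noncentral chi-square formula gives 25%, 41% and 59% for the first row and 75%, 98% and 100% for the third, in agreement. With 405 providers (an assumed 25% loss) the simulated range is 24% to 100%.

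**Center-level determinant.** Take a correlation of 0.5 with the center part of baseline fidelity and an ICC of 0.1 (both assumed). The correlation with the individual score is 0.5 × sqrt(0.1) = 0.158, and the same formula gives 38%, 67% and 88%. A simulation with 90 clusters of six (2,000 runs) gave 40%, 63% and 86%.

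**With baseline forced in.** Selection is 14-18% in every provider-level setting, the nominal AIC rate. If baseline is measured with reliability 0.87 (borrowing the rating ICC), it is 16-42%, still below the unadjusted rate in every setting.

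**Interactions.** The two-degree-of-freedom determinant-by-strategy term is selected in 12-16% of runs without baseline, against a nominal P(chi-square on 2 df > 4) = 13.5%. There is no sign of bias.

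**Precision.** For provider-level terms, adjustment can remove up to rho² of the residual variance: 9%, 25% and 49% at rho = 0.3, 0.5 and 0.7. For center-level terms the gain depends on the between-center correlation, which the document does not give.

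**Change score.** With 8-month minus baseline as the outcome, the same irrelevant determinant was selected in 29-100% of runs, because of regression to the mean.

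**The case against.** **Silence is not exclusion.** The section is three sentences in a journal article. It names no strategy main effect and no center random effect either, so forced covariates may simply be left to the full plan. Elsewhere the article names an outcome at 8 months while its model includes baseline. This has weight, but the section does state the outcome, the candidate set and the selection rule, and the mediation section writes out the baseline covariate for the same outcome. As worded, baseline fidelity does not enter.

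**Success may mean attained fidelity.** The article nowhere defines Aim 2 success as gain. If prior EBP experience raises 8-month fidelity through skill at entry, it is a real determinant of the level reached, and adjustment removes that path. This stands. Calling a selection spurious presupposes that success means fidelity given entry skill.

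**The moderation question is hardly touched.** Correct: interactions are not biased.

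**The size is assumed.** Also correct. The correlations are not in the document, and the rates come from adding one term, whereas the plan searches many, some probably correlated with each other.

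A reader might go further and infer that Aim 2 is the only analysis to take the 8-month level as outcome. It is not, since the mediation analysis does so too; the difference is the adjustment. Nor does the document support a claim that the advice on matching strategy to center would be biased.

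**Conclusion.** The point holds for determinant main effects. As written, the Aim 2 search omits a baseline score that the trial collects and that its other analyses of provider fidelity take into account. Traits that go with entry skill can therefore be selected well above the nominal AIC rate, even at a weak assumed determinant-baseline correlation of 0.1. The size rests on the two assumed correlations and on single-term models, and the return to about 16% also requires an error-free baseline. The primary comparison and the sample size are unaffected. The change is worth making because it is nearly free and bears on the main-effect results of one of three stated aims.

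**What to change.** In the Moderation analyses section, state that baseline simulated-practice fidelity and implementation strategy are in the model at every step and cannot be removed, and that determinants and their interactions with strategy are selected around them. Do not substitute a change score. In the re-runs, force in the baseline value of each secondary outcome that has a baseline wave in Table 1, such as confidence with and use of skills; reach and maintenance start at 4 months. Report main effects as determinants of 8-month fidelity given entry skill.

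The cost is a sentence or two and one degree of freedom for the baseline term. No new data are needed: the assessment is already scheduled at baseline, and "To be eligible to attend the training, mental health providers must provide consent and complete the baseline survey". A rule is needed for providers whose baseline fidelity score is missing, because the article states multiple imputation only for the client effectiveness analysis. Any effect of a determinant that acts through entry skill will no longer be counted. If that effect is also of interest, an unadjusted model can be shown beside the adjusted one and labeled as describing attained fidelity.

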#### Effectiveness outcome analysis

We will summarize client characteristics — including age, gender, and race/ethnicity —overall and by implementation strategy and assess for baseline imbalances. We will then compare client mental health between Materials Only and Direct Training and between Direct Training and Local Supervision. The primary effectiveness outcome is the Patient Health Questionnaire– 9 at 8-month follow-up. In intent-to-treat analyses, we will use a mixed-effects model [93] and the identity link function to evaluate the effect of implementation strategies. The fixed effects include time and the time × implementation strategy interaction; random effects include center and within-client repeated measures. We will use the robust score test to assess whether the interaction terms are significantly different across and between the three strategies. We will use the inverse probability weighting method [99] to adjust for any selection bias due to loss to follow-up. For secondary outcomes (i.e., GAD-7, DUDIT-C, AUDIT-C, LGBIS, R-UCLA, and DERS-SF), we will also use mixed effects models and compare strategies with a 0.05 Type I error rate. In sensitivity analyses, to account for possible imbalances of client factors across the small number of clusters, we will adjust for these factors (e.g., age, gender, race/ethnicity) as well as center-level covariates (e.g., rurality, size) along with time and implementation strategies. We will use multiple imputation [100] to handle loss to follow-up and missing covariate data.

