We hypothesize that these three additive training implementation strategies will predict respective graduated increases in implementation success at 4-, 8-, 12-, and 24-months post-training (see Figs. 1 and [67]). That is, we predict that reach, effectiveness, adoption, implementation, and maintenance will be higher in the Local Supervision condition relative to the Direct Training condition and that the Direct Training condition’s implementation outcomes will be higher than the Materials Only condition. Drawing on theories of organizational [68, 69] and provider [70–73] change, we also hypothesize that organizational (e.g., shared norms of the importance of EBP) and provider (e.g., self-efficacy for EBP delivery) factors will mediate the stronger impact of the more intensive training strategies on implementation success and client mental health outcomes. To facilitate this latter aim, in a subset of 15 LGBTQ community centers (five centers per condition), we will compare the three training implementation strategies in terms of client mental health symptom change from before implementation to 4, 8, 12, and 24 months after.

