### Randomization

Upon receiving 90 signed memoranda of understanding, the 90 LGBTQ community centers will be randomized in a 1:1:1 ratio to receive one of the three implementation strategies. Randomization will be stratified by director report of anticipated staff participation. Specifically, high-attendance centers will be operationalized as those with greater than the median number of anticipated providers across the 90 enrolled centers whereas low-attendance centers will be operationalized as those that anticipate fewer than the median number of providers per center. Centers whose anticipated number of providers is at the median will be randomly and evenly divided across the two groups. The 15 effectiveness centers will be randomized separately to ensure their equal distribution across the three implementation strategies. Randomization allocation will be generated by the study statistician and assigned by the study coordinator. All participants and study staff will be unmasked to condition assignment, as necessitated by the study design.

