##### Sample size justification

We expect to collect mental health data from at least 52 clients in each of the 15 centers (*N* = 780). Power was computed to test the null hypotheses of no difference in outcomes between Materials Only and Direct Training and between Direct Training and Local Supervision in a cluster randomized trial. The standardized change in the primary outcomes (PHQ-9) over 8 months was estimated as 0.92 (est. = −0.79 [0.74]), for Local Supervision, the strategy used in a randomized controlled trial in which LGBTQ-affirmative CBT study therapists received ongoing supervision [48]. With a 0.05 Type I error rate, we have 80% power to detect an effect size of *d* = 0.33–0.37 for 8-month change, assuming a between-center ICC as large as 0.01 and loss to follow-up of 25%. In other words, we will have 80% power to detect the difference between Direct Training and Local Supervision when the standardized change for Direct Training is at most 0.55–0.59. Further, assuming that the standardized change in the outcome is 0.54 for Direct Training, we have 80% power to detect the difference between Materials Only and Direct Training when the standardized change in PHQ-9 is 0.18–0.26 or less for Materials Only.

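### Aim 3 applies the robust score test to 15 centers with no small-sample reference: with the usual chi-square the overall test runs at about 2.4–2.9% instead of 5%, which costs power mainly when effects are modest or only one step works

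*Protocol article*

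**What the plan says.** Under Effectiveness outcome analysis, PHQ-9 at 8 months is analysed with a mixed-effects model. Time and time × strategy are fixed effects; center and within-client repeated measures are random. On the test it says: "We will use the robust score test to assess whether the interaction terms are significantly different across and between the three strategies". So both an overall and pairwise tests are planned. The same test is named for the 90-center Aim 1 under Provider implementation fidelity outcome analyses.

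Aim 3 is run "in a subset of 15 LGBTQ community centers (five centers per condition"), and Randomization adds: "The 15 effectiveness centers will be randomized separately to ensure their equal distribution across the three implementation strategies". The low cluster count is acknowledged once, as a reason for covariate adjustment in sensitivity analyses: "to account for possible imbalances of client factors across the small number of clusters". It is not linked to the reference distribution of the test.

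The Aim 3 Sample size justification says "We expect to collect mental health data from at least 52 clients in each of the 15 centers" and claims "80% power to detect an effect size of *d* = 0.33–0.37 for 8-month change". That claim rests on an ICC of up to 0.01 and a 25% loss of clients. It covers the two adjacent pairwise contrasts; no power is stated for the overall test.

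**The concern.** A cluster-robust score test estimates its variance from the spread of the center-level score contributions. Its chi-square reference is justified when centers are many. That is reasonable for 90 centers but doubtful for 15, with five per strategy.

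The test across the three strategies would then not have its nominal level on the primary effectiveness outcome. Because it errs on the conservative side, the cost is missed differences rather than false positives.

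**Working it through.** **Inputs.** From the article: 15 centers, five per strategy; 52 clients per center; 25% loss; ICC 0.01; Type I error 0.05. Assumed: two-sided tests, equal center sizes unless noted, a chi-square reference, and the overall test read as two interaction terms at 8 months (2 df).

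**Analysed numbers.** 52 × 0.75 = 39 per center; 5 × 39 = 195 per strategy.

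**The plan's own figure.**
- Design effect: 1 + (39 − 1) × 0.01 = 1.38.
- SE of a pairwise difference: √(2 × 1.38/195) = 0.119.
- Detectable d at 80% power, normal reference: (1.960 + 0.842) × 0.119 = 0.333.

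This reproduces the lower end of 0.33–0.37. The article does not say what drives the range. Two variants come close to the upper end: a normal reference at 0.025 gives 0.367, and t on 12 df at 0.05 gives 0.363. With t on 8 df the value is 0.381.

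**Size of the pairwise test.** With equal centers this is exact. For 10 centers the score statistic is T = 10R², where R² is the share of between-center variation explained by strategy. T > 3.841 means R² > 0.3841, which is F(1,8) > 8 × 0.3841/0.6159 = 4.99. The tail probability is 0.056.

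**Size of the overall test.** This was simulated. Center mean changes were drawn with variance 0.01 + 0.99/39 = 0.0354. The statistic U′(Σuu′)⁻¹U was compared with the chi-square(2) value 5.991. Rejection under the null was 2.8–2.9% with equal centers and 2.4–2.9% with unequal centers, against 5.0% for F(2,12). A repeated-measures version of the stated model (52 clients at baseline, 39 at follow-up, within-client correlation 0.5 assumed) gave about the same: 2.8–2.9% at ICC 0.01.

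**Power of the overall test**, ICC 0.01, 39 per center. The F(2,12) noncentrality is 5 × Σ(effect − mean)²/0.0354; for 0/0/0.37 this is 5 × 0.0913/0.0354 = 12.9, giving 81%.

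| Standardized changes (Materials / Direct / Local) | Robust score, chi-square(2) | F(2,12) | Loss |
|---|---|---|---|
| 0 / 0 / 0.33 | 53–54% | 71% | 17–18 points |
| 0 / 0 / 0.37 | 65% | 81% | 16 points |
| 0 / 0.2 / 0.4 | 58% | 76% | 18 points |
| 0.18 / 0.55 / 0.92 (article) | 99% | 99.9% | about 1 point |
| 0.26 / 0.54 / 0.92 (article) | 96.5–96.7% | 99.5% | about 3 points |

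The gap has two sources. Resetting the critical value of the score statistic so that its size is 5% gives 65% at 0/0/0.33 and 75% at 0/0/0.37. Across the modest scenarios about 8–12 points therefore come from the reference alone. The rest arises because the score statistic takes its variance under the null, so a real strategy difference inflates it.

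**Power of the pairwise test** at d = 0.37: about 79.5% for the score test; 77.7% for t on 8 df and 81.4% for t on 12 df.

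**The case against.** Several points on the other side stand.

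- The article hypothesizes graduated effects. At the values in its sample size section the overall test already has about 97–99% power, so little is lost. A reader might infer a general loss of 10 points or more; the documents support that only for modest or one-step effects. Those cases still matter: the Discussion says the trial should show the minimum training needed, which allows that a step adds little, and the 0.92 comes from a controlled trial with supervised study therapists.
- The contrasts that are introduced and powered are pairwise. Their score tests are slightly liberal and lose no power, so no stated power figure is contradicted.
- A reader might infer that a conservative overall test blocks the pairwise results. No such gatekeeping rule is stated.
- The chi-square reference is inferred, and an analysis plan not shown could add a correction. This limits confidence. But the article does choose the test, gives Aim 3 the same one as the 90-center Aim 1, and notes the few clusters only for covariate imbalance.
- A reader might also take the interaction terms to mean all four follow-ups by two contrasts (8 df). The statistic cannot exceed the number of centers, 15, while the 5% chi-square(8) value is 15.51, so that test could never reject. The stated 8-month endpoint points to the 2-df reading instead; the wording should settle it.

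**Conclusion.** The concern holds in limited form. With a chi-square reference and the 2-df reading at 8 months, the overall Aim 3 test has a true size of about 2.4–2.9% at nominal 5%, and the pairwise tests about 5.6%. Relative to F(2,12), the overall test loses about 16–18 points of power when one step works or the steps are modest, and about 1–3 points under the article's graded effects. The powered pairwise contrasts lose none.

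These figures rest on 39 analysed clients per center and ICC 0.01. If the ICC were higher than the article assumes, the graded scenarios would suffer too: at an assumed 0.05 they give 82% against 93% (0.18/0.55/0.92) and 71% against 86% (0.26/0.54/0.92).

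**What to change.** For Aim 3, keep the mixed model and change the reference:

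- **Overall test.** State that it concerns the two strategy interaction terms at 8 months, and refer it to F on (2, 12) df or to a re-randomization of the 15 centers that follows the 5/5/5 scheme actually used.
- **Pairwise tests.** For each contrast use t with one pre-stated center-based df, or a two-arm re-randomization of the 10 centers involved (252 equal splits if unrestricted) with the pairwise difference as the statistic. The three-arm statistic does not test a pair, and 8 and 12 df are not interchangeable.
- **If re-randomization is chosen,** say how the inverse probability weights and clients enrolled after baseline enter the statistic.
- **Aim 1.** Keep the large-sample robust score test for the 90 centers.

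The cost is wording and some programming; data and design do not change. Pairwise size returns from about 5.6% to 5%. With t on 8 df, pairwise power at d = 0.37 falls from about 79.5% to about 77.7%. The Aim 3 detectable effect should be restated to match: about 0.38 with 8 df or 0.36 with 12 df.

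### The Aim 3 sensitivity analysis for imbalance reads as main-effect adjustment, which does little about an imbalanced factor that predicts change in PHQ-9

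*Protocol article*

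**What the plan says.** All of this is in the protocol article, under Effectiveness outcome analysis, unless another section is named.

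- Outcome: "The primary effectiveness outcome is the Patient Health Questionnaire– 9 at 8-month follow-up".
- Primary model: "The fixed effects include time and the time × implementation strategy interaction; random effects include center and within-client repeated measures". No strategy main effect is listed.
- Test: the robust score test is used to "assess whether the interaction terms are significantly different across and between the three strategies". The effect of interest is therefore a difference in change.
- Purpose of the sensitivity analysis: "In sensitivity analyses, to account for possible imbalances of client factors across the small number of clusters".
- Form of the sensitivity analysis: "we will adjust for these factors (e.g., age, gender, race/ethnicity) as well as center-level covariates (e.g., rurality, size) along with time and implementation strategies".

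The Background gives five centers per condition for this aim. The sample size section for this outcome expects at least 52 clients per center and 25% loss to follow-up, and takes a between-center ICC of up to 0.01. The Clients section adds that new clients enter at every later assessment.

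**The concern.** A covariate that does not vary over time, entered as a main effect, shifts a client's baseline and follow-up scores by the same amount. The tested quantity is a difference in change. If an arm has more clients of a kind who improve faster or slower whatever the training, a main effect for that characteristic cannot represent the difference in improvement. Only a covariate × time term can.

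With five centers per arm, chance imbalance is a real threat, and the article says as much. Randomizing the 15 centers separately secures equal numbers per strategy, but not balance on client mix or rurality. Inverse probability weighting and multiple imputation deal with loss to follow-up and missing data. The covariate-adjusted analysis is thus the only one in the article aimed at imbalance. If its estimate barely moves, readers will take that as evidence that imbalance does not explain the result.

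**Working it through.** **1. The plan's own figure, used only as a yardstick.** Clients per arm after loss: 5 × 52 × 0.75 = 195, or 39 per center. Design effect: 1 + (39 − 1) × 0.01 = 1.38. Detectable difference at 80% power: (1.960 + 0.842) × √(2 × 1.38 / 195) = 0.333 at two-sided 0.05. At 0.025 it is (2.241 + 0.842) × √(2 × 1.38 / 195) = 0.367. The stated 0.33–0.37 is reproduced.

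**2. Set-up for the bias.** These are assumptions, not figures from the documents: two arms of five centers, 50 clients per center, five assessments, unit variance, center ICC 0.01, and within-client correlation ρ = 0.6 (range 0.4–0.8). There is no true strategy effect. A binary factor X differs in prevalence by 0.40 between arms and has an effect of 1 SD, either on level (equal at all times) or on change (0 at baseline, 1 at each follow-up). The bias is the expected 8-month time × strategy coefficient from generalized least squares.

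**3. With a strategy main effect and complete data.** The estimate is the difference between arms in mean change. A time-constant term for X cancels. For X acting on change, the bias is 0.40 × 1 = 0.40 before adjustment and 0.40 after it, so 100% remains.

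**4. With the fixed effects as written (arms share one baseline mean).** The estimate is D8 − r × D0, where D8 and D0 are the arm differences at 8 months and baseline, and r is the correlation of a center's mean between the two times:

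r = [0.01 + (ρ − 0.01)/50] / [0.01 + 0.99/50] = 0.0218 / 0.0298 = 0.732 at ρ = 0.6.

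- X on level only: D0 = D8 = 0.40, so the bias is 0.40 × (1 − 0.732) = 0.107. A main effect for X removes it fully.
- X on change only: D0 = 0 and D8 = 0.40, so the bias is 0.40. The fitted main effect is a compromise between 0 at baseline and 1 at follow-up, and it removes only 0.079. That leaves 0.321, and 0.321 / 0.40 = 80%.

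**5. Results under the fixed effects as written, client-level factor.**

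| Scenario | X acts on | Unadjusted | X main effect | X and X × time |
|---|---|---|---|---|
| Closed, ρ = 0.6 | level | 0.107 | 0.000 | 0.000 |
| Closed, ρ = 0.6 | change | 0.400 | 0.321 (80%) | 0.000 |
| Closed, ρ = 0.4 | change | 0.400 | 0.279 (70%) | 0.000 |
| Closed, ρ = 0.8 | change | 0.400 | 0.361 (90%) | 0.000 |
| Closed, 25% loss, ρ = 0.6 | change | 0.398 | 0.326 (82%) | 0.000 |
| Open cohort, ρ = 0.6 | change | 0.400 | 0.271 (68%) | 0.000 |
| Closed, ρ = 0.6 | both equally | 0.507 | 0.321 (63%) | 0.000 |
| Open, imbalance in new clients only | change | 0.101 | 0.009 (9%) | 0.000 |

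A center-level X behaves in the same way: 0.326 of 0.400 remains in the closed cohort (81%) and 0.281 of 0.400 in the open one (70%).

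**6. Size at less extreme values.** The 1 SD effect above is there to show the share remaining, not a plausible size. Bias is the effect on change times the imbalance:

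- 0.3 SD per SD with a 0.5 SD imbalance gives 0.15 SD, which is 0.15/0.37 = 41% to 0.15/0.33 = 45% of the detectable difference. In a two-time calculation with ρ from 0.4 to 0.6, main-effect adjustment leaves 0.118–0.129 (79–86%) under the fixed effects as written, and 0.15 with a strategy main effect.
- 0.1 SD per SD with a 0.2 SD imbalance gives 0.02 SD, about 5–6% of the detectable difference.
- For a trait held by one of five centers in one arm and three of five in the other, the trait variance is 0.4 × 0.6 = 0.24. If the plan's ICC ceiling of 0.01 holds for change and the trait explains all of it, its effect is √(0.01/0.24) = 0.20 SD and the bias is 0.20 × 0.40 = 0.08 SD.

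**The case against.** The strongest reply is that the article never says main effects only. The sentence on the sensitivity analysis also leaves out the time × strategy term, which must be in the model, so it is shorthand. The exact form of covariates is often left to a fuller document. This stands in part: main effects are an inference. It is still the natural one, because the article writes interactions out where it means them, for strategy with time in both outcome analyses and for determinants with strategy in the moderation analyses.

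A reader might go further and infer that the adjustment leaves most of any imbalance bias in place, will nearly always agree with the primary result, and so falsely reassures. The documents do not support that:

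- Under the fixed effects as written, imbalance in a factor that affects only PHQ-9 level does bias the contrast, and main-effect adjustment removes all of that bias.
- When a factor acts on both level and change, the estimate visibly moves (0.51 to 0.32 above).
- When the imbalance arises only among newly enrolled clients, nearly all of it is removed.
- An exactly unchanged estimate requires a strategy main effect, which the article does not list, and complete data, which the article does not expect.

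It is also fair that the bias sizes come from assumed inputs and can be negligible, and that this is a sensitivity analysis for Aim 3 while the trial's primary outcome is provider fidelity.

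**Conclusion.** The point holds in a limited form. The tested effect is an interaction with time, and the imbalance adjustment as worded contains no covariate × time term. If it is fitted as main effects, it corrects for factors that affect only the level of PHQ-9. For an imbalanced factor that predicts change, it leaves about 70–90% of the bias under the fixed effects as written (68% in the open-cohort case examined), and all of it with a strategy main effect and complete data. Those shares depend on the model form, within-client correlation and cohort structure. The absolute bias rests on assumed imbalance and effect sizes, and ranges here from 0.02 to 0.15 SD for a client factor. Agreement with the primary analysis would be weak reassurance about this kind of imbalance. It does not follow that the analysis is uninformative or bound to mislead. The change is worth making because it is cheap and this is the only analysis directed at imbalance.

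**What to change.** In the sensitivity model, enter each listed client factor together with its interaction with time. Limit center-level covariates to one or two, named in advance, each with its time interaction, since 15 centers less 3 strategy means leave only 12 center-level degrees of freedom. State at the same time whether the model includes a strategy main effect, because the behavior of the adjustment depends on it.

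A regression of 8-month PHQ-9 on strategy, baseline PHQ-9 and the factors can be added as a further check. It is not equivalent: it uses only clients with a baseline score, so it drops those who enroll later.

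The cost is a sentence or two of wording, extra parameters and a somewhat wider interval. With five assessments and categorical time, each covariate degree of freedom adds four interaction terms, so multi-category factors such as gender and race/ethnicity may need sensible grouping. The primary analysis is unaffected.
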